## 1 ABBREVIATIONS

|        |                                                            |
|--------|------------------------------------------------------------|
| AE     | Adverse event                                              |
| ALT    | Alanine Transaminase                                       |
| AML    | Acute Myeloid Leukemia                                     |
| AMLCG  | AML Cooperative Group                                      |
| AP     | Alkaline phosphatase                                       |
| APL    | Acute promyelocytic leukaemia                              |
| AR     | Adverse reaction                                           |
| AraC   | Cytosine arabinoside                                       |
| AST    | Aspartate Transaminase                                     |
| ATIII  | Antithrombin III                                           |
| AUC    | Area under Curve                                           |
| bFGF   | Basic Fibroblast Growth Factor                             |
| CBC    | Complete Blood Count                                       |
| CR     | Complete Remission                                         |
| CRc    | Complete cytogenetic remission                             |
| CRi    | Complete Remission with incomplete Neutrophil Recovery     |
| CRm    | Complete moleculargenetic remission                        |
| CRp    | Complete Remission with incomplete Platelet Recovery       |
| CRF    | Case report form                                           |
| CTCAE  | Common Terminology Criteria for Adverse Events             |
| CYP    | Cytochrom P                                                |
| DL     | Dose Level                                                 |
| DLT    | Dose Limiting Toxicity                                     |
| DNA    | Desoxyribonucleic acid                                     |
| ECG    | Electrocardiogram                                          |
| ECOG   | Eastern Cooperative Oncology Group                         |
| FAB    | French-American-British cooperative group                  |
| FGF    | Fibroblast Growth Factor                                   |
| Flt    | Fms like tyrosine kinase                                   |
| FISH   | Fluorescence in situ hybridization                         |
| GCP    | Good Clinical Practice                                     |
| G-CSF  | Granulocyte Colony Stimulating Factor                      |

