### 3.2.2 Phase II

Primary endpoint:

- to evaluate the overall response rate (ORR, consisting of: CR, CRp and CRi as defined by IWG criteria) of the whole study population

Secondary endpoints:

- to compare the ORR rate of the Flt3-mutated patients versus the Flt3-wildtype patients and within different cytogenetic risk groups
- to evaluate the CR rate of the whole study population
- to compare the CR rate of the Flt3-mutated patients versus the Flt3-wildtype patients and within different cytogenetic risk groups
- to evaluate the one-year overall survival (OS) of the whole study population

---

 response criteria by the International Working Group (IWG) are defined as:

- Complete remission (CR): less than 5% bone marrow blasts and regeneration of both peripheral neutrophils to  $>1,000/\mu\text{l}$  and platelets to  $>100,000/\mu\text{l}$
- Complete remission with incomplete platelet recovery (CRp): less than 5% bone marrow blasts and regeneration of peripheral neutrophils to  $>1,000/\mu\text{l}$  with a platelet count of  $<100,000/\mu\text{l}$
- Complete remission with incomplete neutrophil recovery (CRi): less than 5% bone marrow blasts with a neutrophil count of  $<1,000/\mu\text{l}$  with or without platelet recovery

- to compare the one-year overall survival (OS) of the Flt3-mutated patients versus the Flt3-wildtype patients and within different cytogenetic risk groups
- to evaluate the relapse-free survival (RFS) of the responding patients
- to evaluate the time to response (CR, CRp or CRi) of the responding patients
- to evaluate the toxicity in the whole study population
- to evaluate the development of biomarkers indicating the course of disease, including genetic, epigenetic, transcriptional, protein and phosphoprotein markers in leukemic blasts, bone marrow, peripheral blood cells, serum and plasma, and bone marrow microvessel density.

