#### 6.3.2 Requested material and shipment modalities

At diagnosis and during follow-up bone marrow evaluations, please collect for central diagnostics and central tissue and serum repository:

|                                                             |                                                                                                                     |
|-------------------------------------------------------------|---------------------------------------------------------------------------------------------------------------------|
| Central cytomorphological review (on request)        | 5 ml bone marrow aspirate in EDTA
at least 4 unstained bone marrow smears
2 unstained peripheral blood smears |
| Central immunophenotyping (on request)               | 6-8 ml heparinized bone marrow                                                                                      |
| Central molecular diagnosisa (on request) | 6-8 ml heparinized bone marrow                                                                                      |
| Central histologyb (mandatory)            | 1 bone marrow biopsy, fixed in 'Kölner Lösung'                                                                      |
| Central cell repository (mandatory)                  | 2 x 6-8 ml heparinized bone marrow
20 ml heparinized peripheral blood
9 ml serum                              |

a At diagnosis. During follow-up only in case of detection of a molecular marker at diagnosis

b At diagnosis and at the time of response confirmation one month after begin of observation period in responding patients

The fixation solution ‘Kölner Lösung’ will be sent to the participating centers at the time of study initiation, every 6 weeks, and additionally upon request ([contact], or [contact]).

Shipment is recommended from Monday through Thursday, if possible in the morning by express delivery or courier to the following addresses:

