#### 8.4.1 Response criteria

Response criteria are defined according to the Revised Recommendations of the International Working Group for Diagnosis, Standardization of Response Criteria, Treatment Outcomes, and Reporting Standards for Therapeutic Trials in Acute Myeloid Leukemia [18].

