##### Responding Patients:

Morphologic complete remission (CR):

- Platelet count >100,000/ $\mu$ l
- Granulocyte count of >1,000/ $\mu$ l
- Bone marrow (aspirate with marrow spicules): < 5% blasts, Absence of Auer rods
- No evidence of persisting leukemia by flow cytometry (Sensitivity: 5%)
- Absence of extramedullary leukemia
- Transfusion independent stable hemoglobin value

Complete remission with incomplete platelet recovery (CRp):

- Granulocyte count of >1,000/ $\mu$ l
- Bone marrow (aspirate with marrow spicules): < 5% blasts, Absence of Auer rods
- No evidence of persisting leukemia by flow cytometry (Sensitivity: 5%)
- Absence of extramedullary leukemia
- Peripheral blood with no blast cells and less than 100,000/ $\mu$ l platelets

Complete remission with incomplete neutrophil recovery (CRi):

- Bone marrow (aspirate with marrow spicules): < 5% blasts, Absence of Auer rods
- No evidence of persisting leukemia by flow cytometry (Sensitivity: 5%)
- Absence of extramedullary leukemia
- Peripheral blood with no blast cells and less than 1,000/ $\mu$ l granulocytes irrespective of the platelet count
- Molecularly negative (no detection of pre-treatment genetic markers with a methodology providing a sensitivity of at least 1:10^3)

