#### Overall response rate (ORR):

Proportion of patients who achieve either a complete remission (CR), a CRp or a CRi, as defined above, at any time point during study participation.

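### The protocol defines CRi, a component of the primary endpoint, in two different ways, so the number of responders and possibly the test result can depend on which section is applied

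*Protocol*

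**What the plan says.** **Objectives.** Section 3.2.2 states the phase II primary endpoint: "to evaluate the overall response rate (ORR, consisting of: CR, CRp and CRi as defined by IWG criteria". Footnote 1 to that line spells the criteria out. For CRi it reads "Complete remission with incomplete neutrophil recovery (CRi): less than 5% bone marrow blasts with a neutrophil count of" less than 1,000/µl, with or without platelet recovery. It contains no molecular condition.

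**Response criteria.** Section 8.4.1 claims the same source: "Response criteria are defined according to the Revised Recommendations of the International Working Group for Diagnosis" and so on. Its lists are longer for all three categories. Under CRi alone, the last item is "Molecularly negative (no detection of pre-treatment genetic markers with a methodology providing a sensitivity of at least" 1:10^3). Under CR alone, the last item is "Transfusion independent stable hemoglobin value". The footnote has neither.

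**Endpoint definition.** Section 8.5 defines ORR as "Proportion of patients who achieve either a complete remission (CR), a CRp or a CRi, as defined above". The nearest earlier definitions are those in 8.4.1.

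**Molecular testing.** Molecular analyses are listed before treatment (6.1.1). The evaluations during treatment (6.1.2), those during observation of responders (6.1.4) and Table 2 (6.2) name no molecular test at response; marrow and blood are collected for a repository and exploratory research. In 6.3.2 central molecular diagnosis is on request, with the note "During follow-up only in case of detection of a molecular marker at diagnosis". Section 6.3.1 lets sites use their own or any other laboratory and fixes no sensitivity.

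**Other use of the categories.** Section 5.4.1 uses CR, CRp and CRi to decide whether a patient receives a further cycle or moves to observation.

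**The concern.** CRi is one of the three ways to count as a responder in the confirmatory test. If two sections of one protocol disagree on who qualifies, the same patients can give two responder counts.

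The disagreement is more than a matter of detail. The molecular condition falls on the category with the least haematological recovery and not on CR or CRp, so the weakest response faces the strictest disease criterion. The condition also depends on a result that the schedule does not require anyone to obtain.

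The trial is single-arm and response is assessed mainly at the sites, so different centres could resolve the conflict differently. If it is left open, it could also be resolved after responses are known.

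**Working it through.** **1. The two definitions, patient by patient**

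| Patient at response marrow (other 8.4.1 criteria met) | 3.2.2 footnote | 8.4.1 |
|---|---|---|
| <5% blasts, neutrophils <1,000/µl, pre-treatment marker still detected | CRi, responder | Not CRi. Not PR, which needs 5–25% blasts. Stable disease fits only doubtfully |
| Same counts, marker at diagnosis, no molecular result | CRi, responder | Cannot be decided |
| Same counts, no marker at diagnosis | CRi, responder | Not stated; could be read as meeting the condition |
| <5% blasts, neutrophils >1,000/µl, platelets >100,000/µl, still needs red cells | CR, responder | Not CR, CRp or CRi; not PR; not stable disease |

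The first three rows are the CRi conflict. The fourth is the related haemoglobin mismatch.

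**2. The plan's own sample size**

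Inputs from 8.1 and 8.2: null 25%; expected ORR 0.50 × 0.13 + 0.35 × 0.87 = 0.3695, stated as 37%; one-sided α = 0.025; power 80%; 111 evaluable and 122 recruited; exact binomial test, ITT.

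Normal approximation:

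n = [(z₀.₉₇₅ √(p₀q₀) + z₀.₈₀ √(p₁q₁)) / (p₁ − p₀)]²

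With p₁ = 0.3695 this gives 110.28, so 111. The stated figure reproduces.

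**3. Rejection limit of the planned exact test**

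- n = 122: reject at 41 or more responders; actual α = 0.0206; power at 37% = 0.807.
- n = 111: reject at 38 or more; actual α = 0.0186; power at 37% = 0.757.

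The protocol states neither limit; both follow from the test and α it names. The 122 denominator fits the ITT rule in 8.2, and 111 is the evaluable number in 8.1.

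**4. How far a reclassification can move the result**

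- At n = 122 and 37%, about 0.37 × 122 = 45 responders are expected (p = 0.0024). Removing 5 leaves 40 (p = 0.033), which misses 0.025.
- At n = 111, about 41 are expected (p = 0.0035). Removing 4 leaves 37 (p = 0.030), which also misses.

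**5. Illustrative power at n = 122**

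Assumption: 37% is the ORR under the footnote, and some points of it are CRi patients who are marker-positive or untested and so are not counted under 8.4.1.

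| Points lost | ORR under 8.4.1 | P(X ≥ 41) |
|---|---|---|
| 0 | 37% | 0.807 |
| 2 (0.02 × 122 ≈ 2 patients) | 35% | 0.659 |
| 4 (0.04 × 122 ≈ 5 patients) | 33% | 0.477 |

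Equivalently, let s be the CRi share of responders and m the fraction of those not counted, so that ORR under 8.4.1 = 37% × (1 − s·m). Power is 0.672 at s·m = 0.05, 0.505 at 0.10 and 0.191 at 0.20. The protocol gives neither s nor m.

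**The case against.** **The footnote is shorthand and 8.4.1 governs.** The footnote is shorter for all three categories, also omitting Auer rods, flow cytometry and extramedullary disease, and 8.5 follows 8.4.1 directly. This is fair as to reading order. But no text gives 8.4.1 precedence, and the primary objective rests on the footnote. A molecular requirement for one category only is a substantive addition, not an abbreviated detail. Even if 8.4.1 governs, the unscheduled test and the unclassified patients remain.

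**Testing is possible.** Sites may run molecular analyses locally or elsewhere, central follow-up testing is available where a marker was found at diagnosis, and material is stored. This stands: the supported statement is that no molecular test at response is mandatory, not that none is available. A reader might infer that every untested CRi is unclassifiable. The wording does not support that, because a patient without a marker at diagnosis can be read as satisfying the condition, although the protocol does not say so.

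**The power loss is assumed.** This stands too. Section 8.1 does not say which definition lies behind the 37%. If it was 8.4.1, applying the footnote raises ORR and no power is lost. A reader might infer that the test result must turn on the choice. It turns only if enough CRi patients are marker-positive or lack a result.

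**Origin of the item.** Because CRm, "Complete moleculargenetic remission", is abbreviated in section 1 but has no criteria in 8.4.1, a reader might conclude that the molecular item is a stray CRm criterion. CRc is also abbreviated there without criteria in 8.4.1, so this stays conjecture.

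**The transfusion-dependent patient.** A reader might say that 8.4.1 makes this patient a treatment failure. It does not; the patient fits no category and so simply drops out of ORR. Since response counts at any time on study, only patients who never become transfusion independent while otherwise meeting CR are affected. The protocol gives no frequency.

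**Conclusion.** The inconsistency is on the face of the protocol and needs correction. One component of the primary endpoint has two definitions that can classify the same patient differently, and the stricter one relies on a test that is not required at response. Patients with no marker at diagnosis or no molecular result have no stated classification.

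The effect on the responder count is possible, not certain. At the planned 37%, about 4 of 111 or 5 of 122 patients changing status would separate a significant from a non-significant result. The fall in power from 81% to 66% or 48% is an illustration. It assumes n = 122, a 37% ORR planned under the footnote, and a loss of 2 or 4 points that no document supplies.

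The haemoglobin mismatch is a smaller defect of the same kind: CR in the footnote, no category in 8.4.1, size unknown.

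A statistical analysis plan would not cure this alone, because sites classify response from the protocol during treatment.

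**What to change.** Before phase II data are seen:

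1. Reconcile footnote 1 of 3.2.2, section 8.4.1 and section 8.5 to one set of CR, CRp and CRi definitions for ORR, and have 8.5 cite that section by number.
2. State whether molecular status enters ORR. If it does not, report it as a separate category outside ORR. If it does, state how patients with no marker at diagnosis and patients with no molecular result are counted.
3. Give the patient who meets all CR criteria except transfusion-independent haemoglobin a stated category for the ORR and CR-rate analyses.
4. Reconcile 5.4.1 with the result, because it uses the same categories to decide on further cycles. Which rule should govern treatment is for the trial's clinicians and is not proposed here.
5. State in 8.1 which definition the 37% refers to.

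Cost: a wording amendment if molecular status stays outside ORR. If it stays inside, a molecular assessment at response with a fixed sensitivity must also be scheduled, which is a new procedure.

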### Treatment failure:

#### Partial Remission (PR):

- Platelet count  $>100,000/\mu\text{l}$
- Granulocyte count of  $>1,000/\mu\text{l}$
- Bone marrow (aspirate with marrow spicules): Decrease of at least 50% in the percentage of blasts to 5% - 25%

Stable disease: Patient survives  $\geq 7$  days post Chemotherapy (CT); persistent AML in blood or bone marrow neither fulfilling the criteria of Partial Remission nor the criteria of disease progression

Disease progression: Patient survives  $\geq 7$  days post Chemotherapy (CT) with any of the following:

- Reappearance of blasts in the peripheral blood or
- raising blast counts in the peripheral blood or
- raising blast counts in bone marrow or
- appearance, reappearance or progression of chloromas, or
- raising lactate dehydrogenase serum level not otherwise explained,

evaluated as significant disease progression by the investigator.

#### Indeterminate cause:

- Patients who die  $< 7$  days post CT; Patients who die  $> 7$  days post CT with no PB blasts, but bone marrow examination not performed or not evaluable; Patients who do not complete the first course of therapy

#### Morphologic relapse:

- Reappearance of blasts post CT in PB or bone marrow

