#### Relapse-free survival (RFS):

Time interval from the first day a leukemia-free state is achieved in patients who achieve a CR / CRi / CRp until relapse or death from any cause, whatever occurs first. For a patient who is not known to have died or have relapsed by the end of follow-up, observation of RFS will be censored on the date the patient was last known to be alive and in CR.

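### Morphologic relapse has no marrow blast threshold and overlaps the <5% remission limit, so relapse-free survival can count events in patients still within remission

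*Protocol*

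**What the plan says.** **Remission.** In section 8.4.1, CR, CRp and CRi share one marrow line: "Bone marrow (aspirate with marrow spicules): < 5% blasts, Absence of Auer rods". The footnote to section 3.2.2 uses the same limit for all three; for CR it reads "less than 5% bone marrow blasts and regeneration of both peripheral neutrophils" with platelet recovery. For CRp and CRi, section 8.4.1 adds a blood line that begins "Peripheral blood with no blast cells and less than". The CR list has no explicit line on blood blasts.

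**Relapse.** Section 8.4.1 defines morphologic relapse in one line: "Reappearance of blasts post CT in PB or bone marrow".

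**Neighbouring definitions.** Partial remission has a marrow band that starts at 5%. Disease progression lists several signs but requires them to be "evaluated as significant disease progression by the investigator".

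**RFS.** Section 3.2.2 lists RFS of responding patients as a secondary phase II endpoint. Section 8.5 runs it "from the first day a leukemia-free state is achieved in patients who achieve a CR / CRi / CRp" to relapse or death. Patients without an event are censored when "last known to be alive and in CR". The protocol does not define a leukemia-free state, and the German synopsis (12.1) names the endpoint differently, as median leukemia-free survival.

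**The concern.** An event definition should not overlap the state whose loss it marks. Here remission tolerates a non-zero marrow blast share below 5%, while relapse needs only that blasts reappear, at any level. The same marrow can satisfy both.

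Two things follow. RFS can be shortened by events that are not a loss of remission by the protocol's own marrow limit. The error may also be hard to undo later. Responders have a marrow every three months (6.1.4), whereas patients counted as relapsed are followed for adverse events and survival, with further visits at the investigator's discretion (6.1.5). Marrows that could have shown continuing remission may therefore not be taken. Morphology is read locally (6.3.3), so each site would have to supply its own threshold.

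The start and censoring rules in section 8.5 have smaller wording faults. One uses an undefined term, and the other names only CR although the endpoint covers CR, CRp and CRi.

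**Working it through.** The protocol gives no figure to reproduce for this point. The check sets the definitions side by side.

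**1. Overlap by marrow blast share** (8.4.1), for a responder whose previous marrow showed no blasts:

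| New marrow | Within remission blast limit (<5%)? | Relapse as written? |
|---|---|---|
| 0% | yes | no |
| 1–4% | yes | yes |
| 5% or more | no | yes |

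The middle row is the contradiction. It concerns the blast-count criterion; full remission also depends on the other listed items, such as Auer rods and flow cytometry. The blood part of the relapse rule creates no such overlap for CRp and CRi, which require blood free of blasts.

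**2. Who is exposed.** Section 8.1 gives the expected response rate as 0.50 × 0.13 + 0.35 × 0.87 = 0.3695, stated as 37%.
- Of 122 recruited: 0.37 × 122 = 45.1, about 45 responders.
- Of 111 evaluable: 0.37 × 111 = 41.1, about 41 responders.

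**3. How the two rules behave on one marrow (illustration only).** Suppose *c* cells are counted and the true blast share is *t*. Both are assumptions; the protocol gives neither. The chance of seeing any blast is 1 − (1 − *t*)^*c*. The chance of a count of at least 5% is the binomial tail P(X ≥ 0.05*c*).

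| *t* | any blast, c = 200 | ≥5%, c = 200 | any blast, c = 500 | ≥5%, c = 500 |
|---|---|---|---|---|
| 1% | 0.866 | 0.000 | 0.993 | 0.000 |
| 2% | 0.982 | 0.008 | 1.000 | 0.000 |
| 3% | 0.998 | 0.081 | 1.000 | 0.010 |
| 4% | 1.000 | 0.281 | 1.000 | 0.152 |

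Under these assumptions a non-zero count is the usual finding in a marrow well inside the remission limit. A 5% threshold is rarely crossed by counting error at 1–2%, though it is not error-free close to the limit. The table does not give a number of false RFS events. The distribution of blast shares among responders is unknown, and a reappearance also presupposes an earlier marrow without blasts.

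**4. Start and censoring** (8.5). The start rule names all three response categories but ties the date to an undefined state. The censoring rule names CR only. Read strictly, an event-free patient who stays in CRp or CRi has no date that fits it; read as remission in general, the rule works.

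**The case against.** The strongest reply is that the relapse line is being read too literally. It is headed morphologic relapse and speaks of reappearance, so a steady 1–3% marrow that already qualified as remission has not relapsed. Section 8.4.1 also says its criteria follow published recommendations, and RFS is a secondary endpoint with no hypothesis or power attached.

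Part of this stands. A stable low count need not be an event, and the impact is limited. The overlap remains, however, for a marrow that goes from no blasts to 2%. A citation does not remove a conflicting line that the protocol writes out itself. Reading reappearance as the return of leukemia adds a criterion the text does not state. Requiring prior absence creates the opposite problem: a rise from 3% to 8% would not clearly be a reappearance. Section 8.2 leaves analysis detail to the SAP, but this is a stated definition in the protocol.

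Stronger inferences are tempting, and the protocol does not support them:

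- **A count of false relapses.** Assuming that 10–30% of remission marrows show a low non-zero count, over three independent marrows per responder, gives 1 − 0.9³ = 0.27 to 1 − 0.7³ = 0.66, or about 12 to 30 of 45. The 10–30% has no source in the protocol, and repeat marrows in one patient are not independent. Three marrows each is also too many for late responders. Observation ends one year after therapy starts, and six undelayed cycles take 6 × 28 = 168 days, leaving 365 − 168 = 197 days.
- **A start rule unusable for CRp and CRi.** It names CR, CRi and CRp. It is ambiguous, and equally so for CR.
- **Bias from an early start.** Under the footnote in 3.2.2, nearly every marrow below 5% already falls into one of the three responses, so the gap would be about zero. The additional conditions in 8.4.1, such as molecular negativity for CRi, could open a gap, but none has been shown.
- **CRp and CRi patients never being in CR.** They can reach it if counts recover, and the censoring phrase can be read as remission.

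**Conclusion.** The point holds for the relapse definition. As written, a responder with 1–4% marrow blasts after a blast-free marrow is both within the remission blast limit and relapsed, so RFS can include events in patients still in remission. This rests on the literal wording and on no outside figure.

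The size that can be stated is exposure: all responders, about 45 of 122 if the planned 37% is met. The number actually misclassified depends on blast shares and local reading habits that the protocol does not give. The overall response rate, its test and the sample size do not depend on the relapse definition.

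The censoring and start wording in section 8.5 are lesser faults. They should be corrected but do not make RFS inoperable.

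**What to change.** In section 8.4.1, define relapse after CR, CRp or CRi as blasts returning in peripheral blood, or a marrow blast share of 5% or more. The marrow limit is then the complement of the protocol's <5% remission limit and agrees with the 5% lower bound for partial remission.

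In section 8.5, make two wording corrections:
- Start RFS on the date CR, CRp or CRi is first documented, replacing the undefined leukemia-free state.
- Censor patients without an event at the last assessment documenting CR, CRp or CRi.

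The German synopsis should use the same endpoint name. The cost is a few lines of text. No new data, visits or procedures are needed, and the sample size stays as planned.

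### Relapse is defined by blasts in blood or marrow only, so an isolated extramedullary recurrence is not an RFS event on its own date and RFS is biased slightly upward

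*Protocol*

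**What the plan says.** All references are to the Protocol.

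- **Remission (8.4.1, responding patients).** CR, CRp and CRi each carry the condition "Absence of extramedullary leukemia".
- **Progression (8.4.1, treatment failure).** The criteria include "appearance, reappearance or progression of chloromas", if the investigator judges the progression significant. The footnotes on leukemia progression in 5.4.2 and 7.1.3.2 also list chloromas.
- **Relapse (8.4.1).** The only relapse definition printed, under the label morphologic relapse, is "Reappearance of blasts post CT in PB or bone marrow".
- **RFS (8.5).** The interval runs from the first leukemia-free day "until relapse or death from any cause, whatever occurs first". Progression is not named as an event. Patients with neither event when follow-up closes fall under the censoring rule, which reads: "observation of RFS will be censored on the date the patient was last known to be alive and in CR".
- **Role (3.2.2).** A phase II secondary objective is "to evaluate the relapse-free survival (RFS) of the responding patients".
- **Follow-up (6.1.4, Table 2 in 6.2).** Responders are followed to death or to one year from the start of therapy. They have monthly blood counts, and marrow aspirate and physical examination every three months. Table 2 also has a physical examination at suspected relapse; the text list in 6.1.3 does not.

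**The concern.** The criteria for entering remission and for leaving it do not match. Extramedullary leukemia prevents a patient from being called a responder, but its return in a responder does not meet the relapse definition. The Protocol foresees the event, since its progression criteria speak of chloromas reappearing, yet that category sits under treatment failure and does not feed RFS.

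At stake is the timing of RFS events in responders. A failure is either recorded later than it happened or replaced by a censored time tied to the failure itself. Such censoring is informative, because the patient leaves the risk set for a reason that bears directly on prognosis. Both routes make RFS look longer than it is.

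**Working it through.** **1. One patient through the text.** A responder develops a chloroma with no blasts in blood or marrow.

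| Rule | Result on that date |
|---|---|
| Remission criteria, 8.4.1 | No longer fulfilled |
| Relapse definition, 8.4.1 | Not fulfilled |
| RFS event, 8.5 | None |

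Three routes follow under 8.5:
- a later blood or marrow relapse: an event, dated late;
- death without such a relapse: an event, dated late;
- neither by the end of follow-up: censored at the last date known to be in CR.

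**2. The Protocol's own figures (8.1).** No figure is given for RFS. The expected ORR is 0.50 × 0.13 + 0.35 × 0.87 = 0.3695, stated as 37%. The sample size reproduces by the normal approximation for one proportion:

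n = [(1.960 × √(0.25 × 0.75) + 0.842 × √(0.3695 × 0.6305)) / (0.3695 − 0.25)]² = 110.3, so 111.

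The relapse definition does not enter this formula.

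**3. Expected responders.** 0.37 × 111 = 41.07 (evaluable patients); 0.37 × 122 = 45.14 (recruited patients).

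**4. Patients affected.** Number = responders × proportion relapsing within follow-up × share of relapses that are isolated extramedullary. The last two are assumptions: 40% to 80%, and 2% to 10%.

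| Responders | Relapse proportion | Share 2% | Share 5% | Share 10% |
|---|---|---|---|---|
| 41.07 | 40% | 0.33 | 0.82 | 1.64 |
| 41.07 | 80% | 0.66 | 1.64 | 3.29 |
| 45.14 | 40% | 0.36 | 0.90 | 1.81 |
| 45.14 | 80% | 0.72 | 1.81 | 3.61 |

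This is roughly 0 to 3 patients; only the most extreme corner reaches 3.6.

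**5. Effect on 6-month RFS.** This comes from a simulation of 400,000 responders per scenario. All of its inputs are assumed:
- exponential RFS with a median of 6 or 9 months;
- 6 to 11 months of follow-up left after response;
- 2%, 5% or 10% of first events isolated extramedullary;
- a median of 3 months from such an event to death or marrow relapse.

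Under the literal text, the later event is used if it falls within follow-up. Otherwise the patient is censored at the recurrence.

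| Median RFS | Share | Counted as event | Literal text | Difference (points) |
|---|---|---|---|---|
| 6 months | 2% | 0.4992 | 0.5036 | 0.4 |
| 6 months | 5% | 0.4998 | 0.5107 | 1.1 |
| 6 months | 10% | 0.5007 | 0.5219 | 2.1 |
| 9 months | 2% | 0.6302 | 0.6336 | 0.3 |
| 9 months | 5% | 0.6306 | 0.6391 | 0.9 |
| 9 months | 10% | 0.6284 | 0.6455 | 1.7 |

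In these scenarios 36% to 40% of the affected patients end up censored. The others have a late event.

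**6. Scale.** With 6-month RFS near 50%, the simple binomial 95% half-width is 1.96 × √(0.25/45) = 14.6 points for 45 responders and 1.96 × √(0.25/41) = 15.3 points for 41.

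**The case against.** The best reply is that the intent is clear. Section 8.5 says relapse, not morphologic relapse. The RFS clock starts at a leukemia-free state, and the German synopsis (12.1) calls the endpoint leukemia-free survival. Section 8.4.1 refers to published working-group criteria, and section 8.2 leaves analysis detail to the SAP. This supports reading the gap as a slip, but it does not supply the missing event. No second relapse definition is printed, the cited criteria cannot be checked here, and the wording that sites have in front of them names blood and marrow only. The point concerns a definition the Protocol does state, not a detail it leaves open.

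A reader might infer that every isolated extramedullary recurrence is censored. The documents do not support that. A later blood or marrow relapse is an event, and the monthly counts and three-monthly marrow are there to find it; death is also an event. Censoring applies only to patients with neither by the end of follow-up.

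A further fair objection is size. RFS is one of several secondary endpoints in a single-arm trial, the Protocol sets no threshold or comparator for it, and the shift is small against a half-width of about 15 points. That stands, and it limits the weight of the point.

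**Conclusion.** The inconsistency is real. Isolated extramedullary recurrence ends remission under 8.4.1 but is not an RFS event on its own date under 8.5. RFS is then dated late or, for some patients, censored at the last date in CR, and the bias is upward.

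The likely effect is small: about 0 to 3 of 41 to 45 responders and up to about 2 percentage points at 6 months. The direction follows from the text. The size depends on the assumed relapse proportion, extramedullary share, median RFS and time to the later event, none of which the Protocol gives.

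It would be wrong to read this as a threat to the primary result. ORR, CR rate, overall survival and the sample size do not use the relapse definition. The point is worth correcting because the correction is short and the error runs in one direction.

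**What to change.** - **Section 8.4.1:** extend the definition with *or appearance or reappearance of extramedullary leukemia (e.g. chloroma)*, and change the label from morphologic relapse to *Relapse*.
- **Section 8.5:** state that such a recurrence is an RFS event on the date it is documented.

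The cost is one line in each section. No new procedure is needed if the event rests on the physical examinations already in Table 2 and on whatever is found clinically. For that reason the wording should not name CNS relapse as a criterion to be actively sought: a three-monthly physical examination cannot be relied on to establish it, and assessing for it would be an added procedure. The list in 6.1.3 can be aligned with Table 2 at the same time. The downside is that RFS becomes slightly less favourable.
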